## Abstract

**Background:**

The Cochrane risk of bias (RoB) tool has been widely embraced by the systematic review community, but several studies have reported that its reliability is low. We aim to investigate whether training of raters, including objective and standardized instructions on how to assess risk of bias, can improve the reliability of this tool. We describe the methods that will be used in this investigation and present an intensive standardized training package for risk of bias assessment that could be used by contributors to the Cochrane Collaboration and other reviewers.

**Methods/Design:**

This is a pilot study. We will first perform a systematic literature review to identify randomized clinical trials (RCTs) that will be used for risk of bias assessment. Using the identified RCTs, we will then do a randomized experiment, where raters will be allocated to two different training schemes: minimal training and intensive standardized training. We will calculate the chance-corrected weighted Kappa with 95% confidence intervals to quantify within- and between-group Kappa agreement for each of the domains of the risk of bias tool. To calculate between-group Kappa agreement, we will use risk of bias assessments from pairs of raters after resolution of disagreements. Between-group Kappa agreement will quantify the agreement between the risk of bias assessment of raters in the training groups and the risk of bias assessment of experienced raters. To compare agreement of raters under different training conditions, we will calculate differences between Kappa values with 95% confidence intervals.

**Discussion:**

This study will investigate whether the reliability of the risk of bias tool can be improved by training raters using standardized instructions for risk of bias assessment. One group of inexperienced raters will receive intensive training on risk of bias assessment and the other will receive minimal training. By including a control group with minimal training, we will attempt to mimic what many review authors commonly have to do, that is—conduct risk of bias assessment in RCTs without much formal training or standardized instructions. If our results indicate that an intense standardized training does improve the reliability of the RoB tool, our study is likely to help improve the quality of risk of bias assessments, which is a central component of evidence synthesis.

**Electronic supplementary material:**

The online version of this article (doi:10.1186/2046-4053-3-144) contains supplementary material, which is available to authorized users.

## Background

Systematic reviews and meta-analyses of randomized clinical trials (RCTs) are central to evidence-based clinical decision-making
[1, 2]. RCTs are considered the gold standard design when assessing the effectiveness of treatment interventions. Appropriately conducted RCTs may eliminate confounding, allowing decision-makers to infer that changes observed in the outcome of interest are causally linked with the experimental intervention.

If results of RCTs included in a meta-analysis are biased, so will the results of the meta-analysis
[3, 4]. To address this problem, it is recommended that the risk of bias in RCTs is taken into consideration when conducting meta-analysis. A method commonly used for this purpose involves the stratification of meta-analyses according to RCTs with low or high risk of bias.

In 2008, the Cochrane Collaboration published a tool and guidelines for the assessment of risk of bias in RCTs
[5, 6]. The risk of bias tool has been widely embraced by the systematic review community
[7]. The items in this tool address six domains of bias, which are classified as low, high, or unclear risk of bias. The selection of domains of bias was based on empirical evidence and theoretical considerations, focusing on methodological issues that are likely to influence the results of RCTs.

Several studies reported that the reliability of the risk of bias tool is low
[8–10]. Reliability of the risk of bias tool can be assessed between two raters of the same research group, when for instance, they assess the risk of bias of RCTs included in a meta-analysis in duplicate. It can also be assessed across research groups, if the risk of bias was assessed for a trial included in two different meta-analyses by two different research groups. Disagreements between two raters of the same research group may be less problematic since they will normally discuss their ratings to come to a consensus. Disagreements between raters from different research groups will be more problematic, for example, if for the same outcome a trial is considered at low risk of bias in one meta-analysis, but is at high risk of bias in another one. Low reliability of risk of bias assessments can then ultimately have repercussions on decision-making and quality of patient care
[11, 12].

We recently found that the reliability of the risk of bias tool might be improved by intensive standardized training of raters
[8]. However, to our knowledge, no formal evaluation of such a training intervention has been performed. We therefore aim to investigate whether training of raters, with objective and standardized instructions on how to assess risk of bias, can improve the within and between pairs of rater reliability of the Cochrane RoB tool. Here, we describe the methods and the intensive standardized training package for risk of bias assessment that will be used in this study.

## Methods/Design

### Study design

This is a pilot study. The first component is a systematic literature review to identify RCTs that will be used for risk of bias assessment. Using the identified RCTs, the second component of our investigation is a randomized experiment, where raters will be allocated to two different levels of training on risk of bias assessment: minimal training and intensive standardized training.

### Literature search and trial selection

We will search PubMed from inception using database-specific search strategy (Figure 
1). We will include every randomized or quasi-randomized clinical trial in patients with knee osteoarthritis that compared a physical therapy intervention to another physical therapy intervention, sham intervention, or no treatment, which assessed patient-reported pain. The following physical therapy interventions will be considered: land-based exercise, aquatic exercise, manual therapy, electric stimulation therapy, and diathermy. We will only consider studies published in English. No further restrictions will be applied. Two raters will screen reports for eligibility independently in duplicate. Disagreements will be resolved by a senior author ([name]).

**Figure 1 Fig1:**
[figure not shown]
**Search strategy.** *Search strategy conducted on PubMed (http://www.ncbi.nlm.nih.gov/pubmed). The search was last updated on 20 March 2014.

### Data extraction

We will use standardized, piloted data extraction forms to extract information on publication year, sample size, and type of intervention. We will assess risk of bias for selected items of the risk of bias tool, namely sequence of generation, allocation concealment, blinding (participants, personnel, and assessors), and incomplete outcome data. Although a potentially important source of bias, we will not assess selective outcome reporting in our study due to feasibility issues with such assessment
[7]. Within pairs of raters, data extraction will be conducted independently and in duplicate. Potential disagreements within pairs of raters will be solved by discussion until consensus is reached.

### Training on risk of bias assessment

Six raters will assess the risk of bias of every included trial. Four of these raters are doctoral students of physical therapy without previous experience in risk of bias assessment, and two raters are experienced risk of bias assessors. The experienced raters have each been involved in over 15 systematic reviews that included methodological quality assessment. We will use simple randomization (computer-generated numbers http://www.randomizer.org/form.htm) to allocate two students to minimal training and two to intensive training. Randomization will be performed remotely by one of the authors ([name]), who had no contact with the students. Students will not be informed to which training group they have been randomized, and they will be instructed not to discuss their training with each other to minimize the risk of ‘contamination’
[5]. After data extraction is completed, we will ask students to guess in which group they were allocated, whether there was any event during data extraction that made them aware of their group allocation, and if this affected their performance in this study.

Minimal training will mimic assessments made by raters without formal training. It will consist of a single lecture for about 60 min on the definition and importance of each of the assessed domains of bias, without specific or standardized instructions on how to conduct the assessment. In this lecture, the raters will learn how the biases could occur in an RCT (for example, staff recruiting patients who are not concealed to allocation may tamper with random allocation sequences), and they will be shown results of empirical investigations that observed the effect of these biases in clinical treatment effects. The raters will be provided with an article, as an optional reading material, that describes the risk of bias tool
[6] as well as chapter 8 of the Cochrane Handbook for Systematic Reviews of Interventions
[5], which specifically addresses the assessment of risk of bias of studies included in a systematic review.

Raters allocated to intensive training will receive the same lecture for about 60 min. In addition, they will receive standardized instructions on how to assess each of the domains (Additional file
1). The standardized instructions were based on the Cochrane Handbook
[5] and adapted as deemed necessary to increase their objectivity and thus minimize misinterpretations for the assessment of trials of physical therapy in patients with knee osteoarthritis. One of the experienced raters ([name]) will discuss these instructions with them and will give them the opportunity to clarify any questions they may have. This rater is an experienced clinical epidemiologist who was trained by one of the authors of the risk of bias tool (PJ) and has been involved in over 20 systematic reviews that included methodological quality assessment. Next, raters will assess risk of bias in a purposively selected sample of ten articles, which will not be part of the final study sample. One of the experienced raters ([name]) will discuss their assessments after five and ten training articles have been assessed. During these sessions, disagreements between the assessment conducted by the experienced rater and the other raters will be identified. The experienced rater will then provide a rationale to justify his assessment, and discussion will take place until all questions are clarified. The assessments of the raters allocated to intensive training will thus be calibrated with the assessments of the experienced rater.

The raters in both groups will be instructed to not discuss their risk of bias assessment with others.

The study protocol was approved by the research ethics committee of the Florida International University (IRB-14-0110). We will obtain written informed consent from each student rater. This study was not registered in PROSPERO.

### Analysis

We will tabulate the characteristics of included trials and the risk of bias assessments of the three groups of raters (minimal training, intensive training, and experienced raters); before and after consensus. We will then calculate the chance-corrected weighted Kappa with 95% confidence intervals to quantify agreement within and between the three groups of raters for each of the domains of the risk of bias tool. To calculate between-group Kappa agreement, we will use risk of bias assessments from pairs of raters after resolution of disagreements. Kappa values range from 0 to 1, with higher values indicating higher agreement between raters. To calculate the weighted Kappa agreement, risk of bias classification will be ordered as follows: low, unclear, and high risk of bias. Criteria proposed by Byrt
[13] will be used to interpret Kappa values. Values between 0.93 and 1.00 represented excellent agreement; 0.81 and 0.92 very good agreement; 0.61 and 0.80 good agreement; 0.41 and 0.60 fair agreement; 0.21 and 0.40 slight agreement, 0.01 and 0.20 poor agreement; and 0.00 or less will be considered to reflect no agreement.

The main outcome of our study is the comparison of the accuracy of assessment across groups, that is, a comparison of the agreement between raters receiving intensive training and experienced raters with the agreement between raters receiving minimal training and experienced raters. To compare agreement of raters under different training conditions, we will calculate the differences between Kappa values for within- and between-group agreement. To address deviations from normal distribution, we will bootstrap the difference in Kappa values using bias correction and acceleration to derive 95% confidence intervals and *P*-values
[14]. Please see Additional file
2 for assumptions used for the power analysis.

To explore whether quality of reporting influences agreement, we will stratify the analysis according to publication date (before the first CONSORT statement revision in 2001 vs 2001
[15] and later; and before the latest CONSORT statement revision in 2010
[16] vs 2010 and later), assuming that reporting quality of RCTs in physical therapy improved after the publication of the CONSORT statement
[17, 18]. To investigate whether methodological quality influences agreement between raters, we will stratify the analysis by trial size (<100 and ≥100 patients randomized per trial arm), assuming that trial size is associated with methodological quality
[19]. A sensitivity analysis will be conducted on larger (≥100 patients randomized per trial arm) trials published after 2010 (i.e. after the latest revision of the CONSORT statement was published). All *P*-values will be two-sided. Analysis will be conducted in STATA, release 13 (StataCorp, College Station, TX).

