Although the standardized instructions were primarily based on the Cochrane Handbook instructions for risk of bias assessment, we added or adapted some of the criteria to facilitate raters’ decision-making in the present investigation. Some of these criteria are not solely based on empirical evidence but also on our own experience with analyses of individual RCTs and meta-analyses of RCTs (Additional file
1). The main example concerns the assessment of incomplete outcome data. To facilitate decision-making, we used thresholds of drop-out rates to define low and high risk of bias for assessing incomplete data. These thresholds were chosen based on evidence that this drop-out rate could be linked to biases
[22, 23]. Moreover, some of these adaptations may not apply to systematic reviews with different research questions. For instance, because outcomes in our sample of physical therapy trials could potentially be influenced by at least some degree of performance bias, blinding of patients and therapists were by definition deemed necessary. Conversely, the Cochrane Handbook recommends that raters first assess the need for patient and therapist blinding in each trial in light of the outcome of interest and to take this information into consideration when assessing the risk of performance bias. Although we fully agree with this recommendation, it was not included in our standardized instructions for the reason explained above.

The low number of raters randomized to intervention groups will be a limitation for the generalizability of our findings. Due to feasibility issues, we included the minimal number of participants needed to calculate Kappa agreements within each study condition. If results of the present investigation indicate that intensive training may indeed improve the reliability of the risk of bias tool, a future study including a larger number of raters could replicate our methods to address this limitation. Generalizability may be further hindered by the characteristics of the trials assessed in our study and of the individual providing the training on risk of bias assessment. Accuracy of the risk of bias assessment could vary if trials with different patient populations, interventions, and outcomes were assessed. Likewise, the quality of the training on the risk of bias assessment may vary according to the skills of the person who provides the training and the method used to deliver such training.

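### If nearly all trials fall in one category for patient or therapist blinding, weighted kappa can be undefined, zero or negative despite high agreement, and the plan names no measure beside it

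*Protocol article*

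**What the plan says.** The protocol article (Analysis) fixes the measure for each domain: "We will then calculate the chance-corrected weighted Kappa with 95% confidence intervals to quantify agreement within and between the three groups of raters". For the weighting, "risk of bias classification will be ordered as follows: low, unclear, and high risk of bias"; the weights themselves are not given. The main outcome compares intensive-versus-experienced with minimal-versus-experienced agreement. It is analysed as a difference in kappas with a bias-corrected and accelerated (BCa) bootstrap. On interpretation the section says "Kappa values range from 0 to 1, with higher values indicating higher agreement between raters", yet its own scale ends with "0.00 or less will be considered to reflect no agreement".

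Under Strengths and limitations, the article explains that in the instructions "blinding of patients and therapists were by definition deemed necessary". The Handbook step of first judging whether blinding is needed is left out: "it was not included in our standardized instructions for the reason explained above". These instructions go to the intensive group: "In addition, they will receive standardized instructions on how to assess each of the domains". The rated items include "blinding (participants, personnel, and assessors), and incomplete outcome data".

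Literature search and trial selection admits land-based and aquatic exercise, manual therapy, electric stimulation and diathermy, compared with another physical therapy, sham or no treatment.

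**The concern.** Kappa measures agreement beyond what the marginal distributions would produce by chance. When almost every trial sits in one category, chance agreement approaches 1 and little is left to measure. The instructions remove the trial-by-trial judgement of need, and many of the eligible therapies are hard to blind. Heavy concentration in *high* is therefore foreseeable for therapist blinding and possible for patient blinding.

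The main contrast is at stake for those items. It could be undefined, show no benefit, or favour the group that agrees less often with the experienced raters. The interpretation scale would then describe near-perfect raw agreement as none. The strata by publication date and trial size are chosen because reporting and methodological quality are assumed to differ between them. Category prevalence may then differ too, and kappa moves with prevalence even when rater performance does not.

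**Working it through.** **Inputs.** From the protocol: weighted kappa, three ordered categories, the interpretation scale and the blinding rule. The text shown gives no number of trials, category distribution or weights, so there is no figure of the plan's own to reproduce. Assumed for illustration: 60 to 150 trials, various shares of *high*, and linear weights 1, 0.5, 0.

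**Formulas.** Kappa = (Po - Pe)/(1 - Pe). Po is the weighted observed agreement and Pe is its expectation from the two sets of marginals. The uniform-chance (Brennan-Prediger) coefficient replaces Pe by the mean of the nine weights: (3×1 + 4×0.5 + 2×0)/9 = 0.556.

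**1. Constant reference, 60 trials, all *high*.**
- Intensive pair all *high*: Po = Pe = 1, so kappa = 0/0. Raw agreement is 100% and the uniform-chance coefficient is 1.00.
- Minimal pair 40 *high*, 15 *unclear*, 5 *low*: Po = (40 + 7.5)/60 = 0.792, and Pe is the same, so kappa = 0.00. Raw agreement is 67%. Uniform-chance: (0.792 - 0.556)/0.444 = 0.53.

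The kappa difference does not exist, while raw agreement differs by 33 percentage points. Against a constant reference, kappa is 0 whether 90% or 50% of ratings agree.

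**2. Nearly constant.** Two ratings each put 58 of 60 trials in *high* and 2 in *low*, and the *low* trials never coincide. Po = 56/60 = 0.933. Pe = (58/60)² + (2/60)² = 0.936. Kappa = -0.03 at 93% raw agreement.

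**3. Reversal.** 100 trials; the reference rates 97 *high* and 3 *low*.
- Intensive: agrees on 95 *high* trials, misses all 3 *low* trials and calls 2 others *low*. Po = 0.95; Pe = 0.98×0.97 + 0.02×0.03 = 0.951; kappa = -0.025.
- Minimal: finds all 3 *low* trials but calls 20 *high* trials *low* and 10 *unclear*. Raw agreement is 70%; Po = 0.75; Pe = 0.707; kappa = 0.15.

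The uniform-chance coefficients are 0.89 and 0.44.

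**4. How skewed must it be?** Kappa by share of *high*:

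| Share *high* | Rater correct on 90%, errors split evenly | 90% agreement, equal marginals | 95% agreement, equal marginals |
|---|---|---|---|
| 80% | 0.75 | 0.69 | 0.84 |
| 90% | 0.61 | 0.44 | 0.72 |
| 95% | 0.45 | -0.05 | 0.47 |

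The second column splits the remaining trials evenly over *low* and *unclear*; the last two use *low* and *high* only. For the rater in the second column, kappa is 0.85 when prevalence is 40/35/25% and 0.40 at 96% *high*; the uniform-chance coefficient stays between 0.83 and 0.85. With 95% agreement and equal marginals, kappa falls to 0.14 at 97% *high*.

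**5. Bootstrap.** If m of n reference ratings are not *high*, a resample has a constant reference with probability (1 - m/n)^n. For n from 60 to 150 this is about 37%, 13% and 5% for m = 1, 2 and 3. In those resamples kappa is 0 or undefined.

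**6. Strata.** If 95% of trials were *high*, a stratum of 10 trials would be all *high* with probability 0.95^10 = 0.60.

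Quadratic weights leave the kappas in steps 1 and 2 unchanged.

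**The case against.** Four objections carry weight.

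- **The rule does not assign a category.** Deeming blinding necessary does not make a trial *high*: a blinded trial can still be *low* and a poorly reported one *unclear*. The mapping is in Additional file 1, which is not shown. Sham comparators, electric stimulation and diathermy leave room for patient-blinded trials. This stands, and it makes the point conditional and strongest for therapist blinding.
- **Scope.** A reader might infer that all blinding items, or the whole main outcome, are compromised. The documents do not support that. The rule names patients and therapists, not assessors, and it does not touch sequence generation, allocation concealment or incomplete outcome data. That the experienced pair follows the rule is itself an inference, drawn from the calibration described under Training on risk of bias assessment.
- **An article condenses.** Ratings will be tabulated before and after consensus, so skew will be visible, and the handling of undefined values could sit in a fuller plan. That is fair. But the article itself fixes the measure, the reading of values at or below zero, and the incorrect range. Tables alone give no interval for the difference in agreement.
- **Kappa keeps comparability and rewards discrimination.** In the reversal example the minimal pair did find the three *low* trials, so its higher kappa is not pure artefact. A uniform-chance coefficient credits raters who use one category throughout. This is why it should stand beside kappa.

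The strata are exploratory, and within a stratum both kappas share the same trials and reference. The caution therefore applies to comparisons between strata.

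**Conclusion.** The concern holds in conditional form. For patient and therapist blinding, above all therapist blinding, the planned kappa difference may mislead if the experienced reference is constant or nearly so, roughly 95% or more in one category. Kappa can then be undefined, zero or negative at raw agreement of 90% or more, and the contrast between training groups can be undefined or reversed. Near 95% the outcome depends on how the errors fall: the examples run from -0.05 to 0.47. At 80 to 90% in one category, kappa ran from 0.44 to 0.84, which is lowered but usable.

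A reader might infer that kappa will certainly fail here. The documents do not support that, because they give neither the category distribution nor the number of trials, and all prevalences above are assumptions. Kappa comparisons across date and size strata should be read with prevalence in mind. One point is unconditional: the stated range of 0 to 1 is wrong, since kappa can be negative, and the section's own scale provides for that.

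**What to change.** In the Analysis section:

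1. For every domain and stratum, report raw agreement and a uniform-chance weighted coefficient (Brennan-Prediger, same weights) beside kappa, with the same BCa bootstrap for the intensive-minus-minimal difference.
2. State that where kappa is undefined because a rating is constant, the contrast is read from these measures, and that a kappa of 0 or less is not labelled as no agreement without them.
3. Correct the stated range of kappa to allow negative values.

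This needs a few sentences, a few lines of code and no new data. Kappa remains the planned measure; I would not add a prevalence cut-off that moves the main conclusion to another coefficient. The downsides are extra columns in the results tables, and a supplementary coefficient that favours raters who place everything in one category, which the text should say.

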### Strengths and limitations

Our study had two major strengths. First, we will include raters completely inexperienced with the risk of bias assessment to investigate the effect of intensive training on the reliability of the risk of bias tool. By including inexperienced raters, we believe we will be more likely to observe an effect of intensive training, if one indeed exists. If raters were already experienced with the risk of bias assessment, there could be limited room for improvement as postulated in a previous study that investigated the effect of training on a similar method for methodological quality assessment
[21]. Second, raters will be randomly allocated to training groups, and central randomization will be performed to conceal the random sequence of allocation. We acknowledge that this approach may not create a balanced distribution of potential confounders across the two training groups due to the low number of individuals randomized, but the group of students randomized will be fairly homogeneous and confounding therefore unlikely.

Our results can potentially be influenced by performance bias. If raters in the control group understand that they are not receiving the best training available in our study, they may feel discouraged to try and perform risk of bias assessments as best as they can. This could in turn lead to an artificially lower reliability of the risk of bias tool with minimal training as compared to intensive training. Alternatively, they could seek additional training elsewhere or be prompted to self-study. To try and minimize the risk of such performance bias, raters will not be informed to which training group they have been randomized, and they will be instructed to not discuss with each other any characteristics of their training. The use of minimal training as a control intervention may lead to an underestimation of the effect of our intensive training, however. Although ‘no training’ could be used as a control intervention instead of minimal training, this could substantially increase the risk of performance bias in our study, as explained above.

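### With two raters per arm and one consensus pair per arm, the bootstrap interval and P-value omit rater-to-rater variation and are too narrow for an effect of training

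*Protocol article*

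**What the plan says.** Under Training on risk of bias assessment, "Six raters will assess the risk of bias of every included trial". Two of the six are experienced raters. The other four are students, and simple randomization is used "to allocate two students to minimal training and two to intensive training".

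Under Analysis, each pair is reduced to one series of ratings: "To calculate between-group Kappa agreement, we will use risk of bias assessments from pairs of raters after resolution of disagreements". The main outcome is "a comparison of the agreement between raters receiving intensive training and experienced raters with the agreement between raters receiving minimal training and experienced raters". For the difference, "we will bootstrap the difference in Kappa values using bias correction and acceleration to derive 95% confidence intervals" together with P-values, and all P-"values will be two-sided". The section does not say what is resampled. It mentions no rater effect, rater-level variance or rater-level resampling.

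Strengths and limitations takes up the number of raters twice. It grants that so few may leave potential confounders unbalanced, but goes on to say that "the group of students randomized will be fairly homogeneous and confounding therefore unlikely". It later says: "The low number of raters randomized to intervention groups will be a limitation for the generalizability of our findings". It does not say that the intervals and P-values leave out variation between raters.

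**The concern.** The rater is the unit that receives training, so the error bars for a training effect should reflect how much raters differ from one another. Here each arm contributes one consensus series, and the main outcome is a difference between two single kappas. Any difference in ability, care or way of reaching consensus between the two student pairs is indistinguishable from an effect of training. Randomization prevents systematic bias in who gets which training, but it does not remove chance imbalance with two per arm, and the planned interval makes no allowance for that imbalance.

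A P-value below 0.05 could therefore arise from ordinary differences between students. The Discussion links a positive result to use of the training package by the Cochrane Collaboration and the wider review community, so a misread P-value on the main outcome would matter.

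**Working it through.** The article states no sample size or power figure (the assumptions are in Additional file 2, which is not shown), so there is none to reproduce.

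**Step 1: what can be resampled.** Inputs from the protocol: four students split 2:2, consensus ratings used for between-group kappa, and the same experienced reference for both arms. Per domain, each trial supplies three ratings: the reference, the intensive pair and the minimal pair. Resampling pairs within an arm is impossible with one pair per arm. Only trials remain, so the bootstrap carries trial sampling error alone. This is an inference from the design; the protocol does not state it.

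**Step 2: which variance is missing.** Let τ be the SD of true kappa between pairs given the same training. The difference D between two independent pairs then has approximately

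Var(D) = σ²(trials) + 2τ².

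The bootstrap estimates the first term. The second cannot be estimated from one pair per arm.

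**Step 3: size, under assumptions.** The protocol gives neither the number of trials nor τ. Simulation settings: no training effect; three ordered categories with frequencies 0.40, 0.35 and 0.25; linear weights; each pair's true kappa drawn from a normal distribution with mean 0.60 and SD τ; BCa bootstrap over trials with 999 resamples; 2,000 simulated studies per cell.

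Share of nominal 95% intervals that exclude zero:

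| Trials | τ = 0 | τ = 0.05 | τ = 0.10 | τ = 0.15 |
|---|---|---|---|---|
| 50 | 5.8% | 9.6% | 19.6% | 30.2% |
| 100 | 5.7% | 13.5% | 27.3% | 39.3% |
| 200 | 5.8% | 15.3% | 38.4% | 55.1% |

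A second BCa simulation at 100 trials gave about 5%, 13% and 26% for τ = 0, 0.05 and 0.10.

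At 100 trials the two error measures compare as follows:

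| τ | True SD of D | Mean bootstrap SE | Ratio |
|---|---|---|---|
| 0 | 0.102 | 0.101 | 1.01 |
| 0.05 | 0.124 | 0.100 | 1.24 |
| 0.10 | 0.173 | 0.099 | 1.74 |
| 0.15 | 0.231 | 0.098 | 2.36 |

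The formula in step 2 agrees: at τ = 0.10, √(0.102² + 2 × 0.10²) = √0.0304 = 0.174, against 0.173 simulated.

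More trials shrink the first term and leave 2τ² untouched. At τ = 0.10 and 200 trials the bootstrap SE falls to 0.071 while the true SD is still 0.159, a ratio of 2.25.

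**Step 4: what the randomization could support.** Four students split 2:2 give C(4,2) = 6 allocations. An allocation and its mirror image have the same absolute difference, so the smallest two-sided randomization P-value is 2/6 = 0.33. This illustrates the design only. Four of the six allocations would need consensus ratings from students who never worked as a pair, so no randomization P-value can be computed for the consensus contrast. One could be computed only for a statistic built from individual pre-consensus kappas.

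**The case against.** The protocol is more candid than a quick reading suggests. It calls itself a pilot. The sentence that calls confounding unlikely begins by conceding possible imbalance. The rater count is explained as the feasible minimum, and a larger rater study is suggested if results look promising. The Discussion's claim about improved reliability is conditional on the results. All of this stands and limits how severely the point should be put.

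The interval is also not invalid in itself. A reader might infer that the bootstrap is simply wrong, but it answers a legitimate narrower question: whether these two pairs differ in agreement with the experienced pair over trials of this kind. The fault lies in using it for an effect of training.

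A reader might also take one of the inflated false-positive rates as the rate this study will have. The documents do not support that, because τ is unknown. Among similar doctoral students it may be small; at τ = 0.05 and 100 trials the rate is about 13%, not 27%.

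The caveats still do not reach the problem. Limited generalizability concerns other raters, whereas even for these four students the effect of training cannot be separated from the difference between pairs. The homogeneity statement amounts to assuming τ near zero, which is the condition the interval needs, and the article offers no data for it. Power assumptions in Additional file 2 cannot supply rater variance that one pair per arm does not contain.

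**Conclusion.** The point holds for the stated aim. For the main contrast, the planned 95% intervals and P-values contain no between-rater variance, so they are too narrow for an effect of training whenever pairs differ for reasons other than training. The direction follows from the design, given the inference that trials are resampled. The size rests on the assumed mean kappa, trial count, rating frequencies, weights and τ: at 100 trials, from about 5% to 6% false positives with no pair differences to 26% to 27% at a between-pair SD of 0.10. The concessions on imbalance and generalizability do not tell the reader that rater variation is excluded from the error bars.

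**What to change.** - State in Analysis that the bootstrap intervals are conditional on these raters and reflect sampling of trials only.
- Drop the P-values for the training contrast. Substituting a randomization P-value is not a remedy: it cannot be computed for the consensus contrast, and one built from individual kappas could not fall below 0.33.
- Report, by domain, each of the four students' pre-consensus kappas against the experienced reference, next to the between-arm difference. Two values per arm show the spread between raters but are too few to estimate its variance well.
- Remove the statement that confounding is unlikely and keep the concession that precedes it.
- Present the result as a descriptive pilot estimate for a larger rater study that has more raters per arm and models rater variance.

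The cost is wording plus four extra kappas per domain, from ratings that will be collected and tabulated anyway. The downside is that the headline result becomes descriptive.
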